## Abstract

**Abstract:**

**Trial Registration:**

ClinicalTrials.gov: NCT00849563

## Background

The judicious use of genetic and genomic information has significant, if untested, potential to enhance the clinical care and prevention of chronic diseases - both indirectly, by contributing to our understanding of disease biology, as well as more directly, by providing additional information to influence providers' screening and treatment recommendations and patients' engagement and health behaviors [1].

Type 2 diabetes represents a highly relevant and important example of a genetically complex chronic disease. Over 20 million people currently suffer from diabetes in the US alone, and more than a million new cases are diagnosed each year [2]. High blood glucose is a leading cause of death around the world [3]. There is strong evidence that lifestyle changes can delay progression to diabetes, even in high-risk individuals, for at least a decade [4]. However, uptake of recommended behaviors appears disappointingly low, as evidenced by skyrocketing rates of obesity in the US and globally, driven by multiple factors [5-7]. Recent reviews of diabetes prevention and screening have thus articulated the need for more effective strategies for increasing patients' motivation and improving adherence to lifestyle changes which have been shown to reduce risk for type 2 diabetes [8,9].

To date, approximately 40 common DNA variants, or single nucleotide polymorphisms (SNPs), have been found to be associated with increased risk for type 2 diabetes [10,11]. One limitation to the broader application of such testing is that the magnitude of increased risk conferred by each variant is relatively small (although there is evidence that testing for these 40 variants can improve reclassification of diabetes risk for individuals under the age of 50 [11]). Thus, genetic risk testing for these variants may not yet offer significant predictive value for individual patients sufficient to alter providers' screening and treatment recommendations. Genetic risk information, however, could have clinical utility in other ways.

Clinical utility (defined as net benefit in improving health outcomes) of genetic testing could be demonstrated through increasing patient activation or positively influencing patient attitudes, beliefs, and health-related behaviors [12]. The relatively scarce research into clinical utility of genetic testing has produced mixed results [13,14]; however, some studies have found evidence that providing results of genetic tests for chronic diseases increases patients' preventive behavior [15,16]. A recent systematic review of the impact of genetic risk information on chronic adult diseases found some psychological benefits of including genetic information in treatment of chronic diseases, but concluded that many gaps in knowledge must be addressed before genetic science can be effectively translated into clinical practice [13].

In this paper, we describe the development, design, and methods of a randomized controlled trial (RCT) designed to assess the clinical utility of incorporating type 2 diabetes genetic risk testing into comprehensive diabetes risk assessments performed in primary care. The intervention tested in this RCT is integrated into a primary care setting and includes a theory-based tool to communicate risk of developing type 2 diabetes to patients. This study does not focus on the predictive utility of the genetic test *per se*; rather, it focuses on whether adding genetic test results to standard risk assessment affects patients' clinical outcomes, behaviors, and perceptions.

### Conceptual framework: Altering patient risk perceptions

A potential role for genetic risk information in disease prevention efforts is described by the Common Sense Model (CSM) of self-regulation of health and illness, adapted by Marteau and Weinman [17] to explain patient responses to health risk information. Health risk information (internal or environmental) informs the cognitive representation of and/or the emotions associated with a health threat, which in turn activates a coping plan, followed by an appraisal of the coping plan [18]. The appraisal then feeds back to update both the representation and coping plan in a continuous, dynamic fashion.

Genetic risk information could provide a distinct type of information to the cognitive representation of type 2 diabetes risk. For instance, the construction of beliefs about personal health risks may be derived in part from an individual's experience of the pattern of disease expression in their families [19]. However, patients may discount family history information because they feel different in crucial ways from affected relatives [20]. Genetic risk information that is specific to the individual cannot be discounted in the same way, and thus may carry added personal significance for patients. Genetic information might engender heightened perceived risk (i.e., anticipated harm if no action is taken), increased emotional response, and then formulation of a coping plan. Accordingly, our hypothesized mechanism of the effect of genetic risk information is that it increases perceived risk, which will in turn increase motivation to engage in coping by increasing preventive health behaviors. Genetic risk information may also serve as a more durable reminder of threat over time, and serve to reinforce the importance of the coping plan through the appraisal process [21].

## Methods/Design

This study is funded with support from The Duke Endowment (Charlotte, NC), approved by the Duke University Health System Institutional Review Board, and registered at ClinicalTrials.gov (NCT00849563).

### Overview

This RCT consists of three study arms (see Figure 1). Study coordinators tell prospective participants about the availability of genetic testing for diabetes risk, and ask them if they would be interested in undergoing such testing as part of a research study. After providing informed consent to participate and having eligibility confirmed, those interested in genetic testing are randomly assigned to undergo *either *a standard risk assessment (SRA) for type 2 diabetes plus upfront disclosure of the results of genetic risk testing (SRA+G), *or *the SRA alone (SRA). (The standard SRA incorporates the conventional risk factors of fasting glucose, body mass index (BMI), race/ethnicity, and age.) Patients not interested in genetic testing for diabetes risk are not randomized and receive only the SRA in a third study arm (No-Test).

**Figure 1 F1:**
[figure not shown]
**Study flow**.

Participants are also asked to complete four study encounters over 13 months: In-person visits at *baseline *and for *risk counseling *(approximately 4-6 weeks after baseline), a remote *3-month survey *(i.e., 3 months after risk counseling), and a *12-month *end-of-study visit. Height and weight (to calculate BMI), waist circumference, fasting plasma glucose and fasting insulin levels are measured at baseline and 12 months. Buccal swabs for DNA collection are obtained from all participants interested in genetic risk testing at the baseline visit. Surveys completed at each encounter will be used to track patients' behavioral and emotional responses to diabetes risk information over time, including perceptions of personal risk for type 2 diabetes. Primary outcomes are changes in insulin resistance and weight; secondary outcomes are changes in diet, physical activity, and waist circumference.

### Settings, eligibility, and recruitment

Patients are recruited in the clinical laboratory waiting areas of two primary care outpatient clinics - one an internal medicine practice, the other a family medicine practice -located in Durham County, North Carolina (NC), in the southeastern United States. These clinics serve a cross-section of Durham residents in terms of age, sex, race, and payor mix, and are affiliated with an academic health system. Durham County itself has a high prevalence of chronic disease and risk factors for disease. In 2007, 9% of all Durham County residents (14% of African-American residents) reported having a diagnosis of diabetes, 30% of residents were obese, and an additional 34% were overweight [22].

Study inclusion criteria are as follows: between the ages of 18 and 81 years; no self-reported history of diabetes; no self-reported history of prior genetic testing for diabetes risk; and not currently pregnant. To reduce the burden of participation, participants in the clinic who are already awaiting a fasting glucose draw or panel of tests that included glucose are invited to participate. Prospective participants are excluded if: they are taking or had taken medications normally used to treat diabetes; if baseline fasting glucose (tested at enrollment) ≥ 7 mmol/L (≥ 126 mg/dL), indicating possible undiagnosed diabetes; if they are not fasting and are unwilling to return for a fasting blood test; if baseline surveys are not completed; or if they cannot provide informed consent unassisted.

Participants will receive $20 for each of the three in-person study visits and are eligible for drawings for additional cash prizes for completing the *3-month survey *and *12-month visit*. In addition, those interested in genetic testing who are randomized to the SRA arm are given the option of receiving their diabetes genetic risk results after completing the *12-month visit *and concluding their participation in the study.

### Randomization

Randomization assignments are made when buccal swab samples are received from the two clinic sites at a central location, by study staff not installed at the clinical sites, and prior to sending the samples off for testing. This arrangement, in addition to obtaining buccal swabs from all participants interested in genetic risk testing, has the effect of blinding both participants *and *study staff at each clinic site to which arm participants have been randomized, until participants return for risk counseling.

### Genetic risk testing

Among the best-studied - and most predictive - SNPs associated with increased risk for developing type 2 diabetes, are two closely linked SNPs (rs7903146 and rs12255372) in the *TCF7L2 *gene; in both, the T allele is the higher-risk variant. More than 30 studies have replicated the finding that these two SNPs in *TCF7L2 *are associated with increased type 2 diabetes risk in White, Asian, and African American populations [23]. Participants in the Diabetes Prevention Program (DPP) study who were TT homozygous (i.e., had two higher-risk variants) at either of the two SNPs in the *TCF7L2 *gene had an increased risk of progression from impaired glucose tolerance to type 2 diabetes compared with participants who were CC and GG homozygous (with hazard ratios = 1.55 and 1.53, respectively) [24].

In the current study, one of these SNPs in the TCF7L2 gene, along with SNPs from three other genes (CDKN2A/2B, CDKAL1, and PPARG), reproducibly found to be associated with increased risk for type 2 diabetes, will be genotyped [10]. DNA is obtained via buccal swab from all participants who consent to genetic risk testing and is sent to a Clinical Laboratory Improvement Amendments (CLIA)-certified laboratory for testing (deCODE genetics, Chicago, IL). The conscious decision to use a commercially-available test from a CLIA-certified laboratory - rather than performing testing in a research laboratory - was made in order to maximize generalizability, and future translation, of any significant study findings.

### Family history

Self-reported family history of type 2 diabetes is assessed by asking respondents to report the number of first-degree (mother, father, brothers and sisters, children) and second-degree (maternal and paternal aunts, uncles, and grandparents) biological relatives with type 2 diabetes. Following the algorithm described in Hariri et al. [25], participants are classified into average, moderate or high familial risk for type 2 diabetes.

### Risk profiling

#### Diabetes risk profile

At the time of their risk counseling visits, all participants receive a pictorial profile indicating their status with respect to individual risk factors for type 2 diabetes (see Figure 2). The profile used in this study was developed by a multi-disciplinary working committee, which included clinicians, genetic counselors, and a risk communication expert.

**Figure 2 F2:**
[figure not shown]
**Risk profile (used to communicate patient risk for developing type 2 diabetes)**.

Age is included as a separate risk factor only for participants over 45 years of age. Race/ethnicity is included only when participants report Hispanic ethnicity, or African-American and/or Native American race, these being groups at elevated risk for type 2 diabetes.

In addition, each risk factor-containing box is color-coded to suggest different degrees of risk and aid in the communication of relative risks to the patient. For example, for the fasting glucose results, the background color would be red if the glucose test result is between 100 and 125 mg/dL, with the notation, "This means that you are 'prediabetic,' which puts you at High Risk for diabetes. You should probably see your doctor to follow up this test result. 1 out of 4 people with a blood sugar this high gets diabetes in the next 3 to 5 years." Conversely, the background color for this section would be yellow if the glucose test result is less than 100, with the notation, "This result falls in the normal range. What this means for your risk for diabetes depends on other risk factors, such as those below." BMI 30 and above (i.e., obese) would be colored red, between 25 and 30 (i.e., overweight) orange, and BMI less than 25 (i.e., normal) yellow. Age greater than 45 years of age and higher-risk race/ethnicity are color-coded orange.

Genetic risk appears on the profile only for participants randomized to receive upfront disclosure of genetic risk testing (i.e., those in the SRA+G arm). This is presented as the number of higher-risk alleles for each of the four SNPs included in the diabetes genetic risk test used in this study (i.e., "You have X out of 8 possible higher-risk DNA changes tested for in four genes linked to higher diabetes risk"). Participants homozygous for the higher-risk TCF7L2 (T) allele are given the additional information that overweight individuals with this genotype and prediabetes have approximately double the risk for progression to type 2 diabetes [24,26].

Participants receiving genetic risk results (SRA+G) are also given the official deCODE test report, which presents a combined genetic risk for type 2 diabetes as an odds ratio with an explanation of these results. Participants' primary healthcare providers are not given copies of either the risk profile or the deCODE test report, and participants are neither encouraged nor discouraged from sharing this information on their own.

### Web-based risk profile generator

Through iterative meetings led by a faculty informatician, specifications were developed to operationalize the profile as a web-based tool. A Web portal was then developed which collects these risk factors in a de-identified manner and generates a PDF risk profile based on these risk factors. The underlying technologies used in this Web portal were Java Server Pages for the Web development, Java for the software engineering, XML for the patient data representation, and XSL-FO in conjunction with the Apache Formatting Objects Processor for the conversion of the XML data into human-readable PDF risk profiles. The XSL-FO stylesheet was generated using commercial software (Altova StyleVision Enterprise Edition).

### Risk counseling

#### Training of embedded clinic staff

Embedded healthcare providers already involved in the clinical care of patients at each site - a clinical pharmacist (who is also a certified diabetes educator, or CDE) and a physician assistant at the family medicine clinic; and a nurse practitioner at the internal medicine clinic - have undergone a 2-hour training to ensure that risk information is consistently and accurately presented in easy-to-understand language and manner, with standardized content. The training session was developed and led by a certified genetic counselor, in consultation with a faculty researcher in risk communication, both of whom have extensive experience in genetic risk communication. Didactic, discussion, and role-playing activities focused on developing a knowledge base and strategies for communicating genetic and non-genetic risk information, as well as counseling regarding desirable lifestyle change [27,28].

#### Delivery of risk assessment results

Risk counseling appointments will be scheduled for each participant with one of the trained embedded healthcare provider(s) at that participant's regular clinic. These appointments will occur approximately 3-6 weeks after the baseline visit, sample collection, and return of genetic testing results (if any). To facilitate uniformity of counseling content, the risk profile described above will be used to guide the order of the visit.

#### Additional resources

Participants are provided with several additional resources to aid in the comprehension of diabetes risk information and implementation of diabetes prevention behaviors, including educational materials on diet, exercise, weight loss, and strategies for lowering risk for type 2 diabetes; a list of online resources compiled from standard diabetes education materials to facilitate active learning about type 2 diabetes, diabetes risk, and diabetes prevention; and the NHGRI publication *A Guide to Your Genome*, a 12-page booklet with information about genome science, genetic tests, and genome research. Participants are also provided with access to an online health portal, The PHD Network (Personal Health Development Network; http://www.activhealth.com). This health portal includes tools for assessing personal health risks for conditions including type 2 diabetes, as well as educational materials, health assessments, and behavioral goal-setting and tracking tools.

### Study measures: Outcomes

Primary clinical outcomes are changes in insulin resistance and weight over 12 months. Change in insulin resistance will be assessed by measuring fasting insulin and serum glucose levels at baseline and 12 months, and calculating the homeostasis model assessment of insulin resistance (HOMA-IR). The HOMA-IR is a widely-used measure of insulin resistance that is tightly correlated with the criterion standard of direct measurement by insulin clamp technique [29,30]. Change in weight will only be analyzed among overweight and obese patients (because healthy-weight patients will presumably not be counseled to lose weight). Weight at 12 months will control for baseline weight; specifically, the 12-month weight outcome variable will be residualized change scores (residuals captured from regressing 12-month weight onto baseline weight).

Secondary clinical outcome measures will be changes in diet, energy expenditure, and waist circumference. Change in diet will be measured using the 16-item dietary subscale from the National Health Interview Survey [31] and change in energy expenditure is measured using the World Health Organization's (WHO) Global Physical Activity Questionnaire [32]. Waist circumference will be measured at baseline and 12 months; the waist is defined as the midpoint between the highest point of the iliac crest and the lowest point of the costal margin at the midaxillary line [33]. All 3-month and 12-month outcome variables will be residualized change scores.

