### Analyses

Data will be analyzed according to intention-to-treat principles. Data will be checked for completeness and the characteristics and frequency of missing data will be described. Missing data values will be imputed as appropriate.

Our primary hypothesis is that patients in the SRA+G arm will have a greater reduction in insulin resistance and lose a greater percentage of their baseline weight after 12 months compared to patients in the SRA arm. We will test these hypotheses with linear multiple regression models with weight or insulin resistance at 12 months as the outcomes (testing a separate model for each outcome) and arm, clinic site, and baseline patient characteristics as explanatory and control variables. We will test our hypothesized mechanism with mediation analysis; specifically, hierarchical linear regression models will test whether effects of the intervention on insulin resistance and weight at 12 months is partially or fully accounted for by perceived risk at 3 months.

Our secondary hypotheses are that patients in the SRA+G group will report significantly healthier dietary changes and will have significantly greater average weekly energy expenditure than patients in the SRA group after 3 months. We will test this hypothesis with linear multiple regression models with behavioral variables at 3 months as the outcomes (testing a separate model for each variable) and arm, clinic site, and baseline patient characteristics as explanatory and control variables. We predict that this difference will narrow, but will still be significant at 12 months; we will test this hypothesis by fitting the same regression model with 12-month behavioral variables as outcomes. In addition, we hypothesize that overweight and obese patients in the SRA+G group, irrespective of diabetes genetic panel test result, will have a greater reduction in waist circumference. Residualized change scores (controlling for baseline values) will be used for 3- and 12-month outcome variables.

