### Power and sample size considerations

Power and sample size estimates are based on the primary study outcomes, percent weight change (from baseline) and change in HOMA-IR, both after 12 months. Based on two studies of low-intensity clinic-based weight loss interventions, we estimate that approximately 20% of patients in the SRA+G arm will lose 5% of their body weight over the course of a year, compared to approximately 10% of patients in the SRA arm [36,37]. Under these assumptions, the mean weight change for participants in the SRA+G arm is estimated to be around 1.7% of baseline body weight, with a standard deviation of approximately 3.9; and the mean weight change to be zero in the SRA arm. We further assume that changes in weight follow normal distributions with equal standard deviations for both groups. Because we are studying a low-intensity informational intervention, for purposes of sample size calculation we will aim for sufficient power to detect a difference in weight change that is 2/3 of the 1.7% difference estimated above. Thus, approximately 198 patients are needed in each group for a two-sided type I error rate of 0.05 and 80% power.

From a number of comparable studies, we conservatively estimate that participants in the SRA+G arm will be able to lower HOMA-IR by 0.5 over the course of a year through lifestyle changes; those in the SRA arm are again assumed to have a mean change of zero. Mean baseline HOMA-IR is estimated to be 2.5 with a standard deviation near 2.0 [38-41]. Using these estimates, 253 patients per group would be required to achieve a significance level of 0.05 with 80% power.

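### The sample size for the primary weight outcome does not allow for restricting that analysis to overweight and obese patients; if 64% qualify, 253 randomised per group gives about 72-74% power

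*Protocol article*

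**What the plan says.** All references are to the protocol article.

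- **Outcomes** (under Study measures). Weight change over 12 months is one of two primary outcomes; the other is insulin resistance by HOMA-IR. For weight the population is fixed: "Change in weight will only be analyzed among overweight and obese patients". The reason given is that patients of healthy weight would presumably not be advised to lose weight. HOMA-IR has no such restriction.
- **Settings, eligibility, and recruitment.** Neither the inclusion nor the exclusion criteria mention BMI. The section describes the county population thus: "30% of residents were obese, and an additional 34% were overweight".
- **Risk profiling.** The profile has a colour category for BMI below 25, so normal-weight participants are expected.
- **Power and sample size considerations.** For weight, the SRA+G mean change is "estimated to be around 1.7% of baseline body weight, with a standard deviation of approximately 3.9", with "the mean weight change to be zero in the SRA arm". The target is "a difference in weight change that is 2/3 of the 1.7% difference estimated above", and the conclusion is "approximately 198 patients are needed in each group for a two-sided type I error rate of 0.05 and 80% power". For HOMA-IR the size is 253 per group. The section does not mention the weight restriction, the expected share of overweight or obese patients, or a final enrolment number.
- **Analyses.** The primary hypothesis is that SRA+G patients will "lose a greater percentage of their baseline weight after 12 months". It is worded for patients in the arm without naming the subgroup. The waist circumference hypothesis in the same section does name overweight and obese patients.

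**The concern.** A sample size has to refer to the patients who enter the analysis. Here the weight analysis excludes everyone of healthy weight, the trial admits them, and the power section neither names the subgroup nor inflates for it. Its assumptions are stated for patients in the two arms, and the weight and HOMA-IR sizes are given in parallel terms although only one of the two outcomes is restricted. A reader could take either number as the size of the arm and attach 80% power to the weight test.

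Weight is one of two primary outcomes, so this affects how a null result is read. If the analysable number is well below 198 per group, the chance of missing the targeted difference exceeds the 20% that the plan implies.

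**Working it through.** **Inputs.** From the power section: SD 3.9, two-sided alpha 0.05, power 80%, difference 2/3 × 1.7 = 1.133 percentage points; for HOMA-IR, difference 0.5 and SD 2.0. From the eligibility section: 30% + 34% = 64% overweight or obese among county residents. Applying that share to trial participants is an assumption.

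**Step 1: reproduce the plan's figures.** Formula: n per group = 2 × (1.96 + 0.8416)² × (SD/difference)².

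- Weight, difference rounded to 1.1: 2 × 7.849 × (3.9/1.1)² = 197.3, so 198. This matches the plan.
- Weight, difference unrounded at 1.133: 185.9, so 186. The plan evidently rounded to 1.1, so both differences are carried forward.
- HOMA-IR: 2 × 7.849 × (2.0/0.5)² = 251.2, so 252. The t-test version gives 252.1, so 253, which matches the plan.

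The printed sizes are therefore correct for analysable patients.

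**Step 2: apply the restriction.** Analysable per group = randomised × share. Power ≈ Φ(difference / (3.9 × √(2/n)) − 1.96).

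- 253 × 0.64 = 161.9. The standard error is 3.9 × √(2/161.9) = 0.433. Power is Φ(2.54 − 1.96) = 0.72 at 1.1 and Φ(2.61 − 1.96) = 0.74 at 1.133.
- 198 × 0.64 = 126.7. The standard error is 0.490. Power is Φ(2.24 − 1.96) = 0.61 at 1.1 and Φ(2.31 − 1.96) = 0.64 at 1.133.

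**Step 3: vary the share**, since the clinic share is not given. Weight power at difference 1.1 / 1.133:

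| Share overweight or obese | 253 randomised per group | 198 randomised per group |
|---|---|---|
| 60% | 69% / 72% | 59% / 61% |
| 64% | 72% / 74% | 61% / 64% |
| 70% | 76% / 78% | 65% / 68% |
| 75% | 78% / 81% | 68% / 71% |
| 80% | 81% / 83% | 71% / 73% |
| 90% | 85% / 87% | 76% / 78% |

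**Step 4: what 80% would need.**

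- Share needed at 253 per group: 186/253 = 73.5% (difference 1.133) to 198/253 = 78.3% (difference 1.1).
- Number to randomise at a 64% share: 186/0.64 = 290.6, so 291, to 198/0.64 = 309.4, so 310 per group.

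No loss to follow-up and no gain from covariate adjustment is included in these figures.

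**The case against.** **198 may already mean analysable patients.** A reader might infer that 198, or 253, counts everyone randomised. The document does not say so: it speaks of patients needed or required in each group, never of patients randomised, and gives no enrolment target. The weight inputs come from weight-loss interventions, which fits a reading of 198 as overweight or obese patients. This stands. It does not remove the gap, because on that reading more than 198 per group must be randomised, possibly more than 253, and the section says neither.

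**64% is not a clinic figure.** It describes county residents in 2007. Trial participants are primary-care patients awaiting a glucose test and free of known diabetes, and the randomised ones also want genetic testing. Their share could be higher or lower. This stands, so a flat statement that the 80% power is not delivered is unsupported: at 253 per group it is reached once about 74-78% qualify.

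**The practical effect may be small.** The target is deliberately two thirds of the expected difference. At the full 1.7, power is Φ(1.7/0.433 − 1.96) ≈ 97% with 162 per group and Φ(1.7/0.490 − 1.96) ≈ 93% with 127. Regression on baseline characteristics may also recover some precision. Both points are fair, but the 80% claim is attached to the reduced difference and takes no credit for adjustment.

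**Loss to follow-up.** A reader might add that there is no dropout allowance. A condensed article commonly leaves that to the full protocol, and the Analyses section provides for imputation, so it forms no part of this point.

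**The hypothesis wording.** The Outcomes section defines the weight population explicitly, so a hypothesis that does not repeat it is loose wording and not a contradiction. That is accepted; aligning it is a tidy-up.

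**Conclusion.** The point holds in conditional form. The arithmetic behind 198 and 253 is sound. What is missing is the link between the weight sample size and the restricted population in which weight will be analysed.

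If the document's only available share, 64%, applies to the trial, the larger stated size of 253 per group gives about 72-74% power for weight. That is a shortfall of 6 to 8 points, or a type II error of 26-28% in place of 20%. If only 198 per group were randomised, power would be 61-64%, but that case is less relevant because HOMA-IR needs 253.

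These figures rest on the 64% assumption, a common SD of 3.9, a difference of 1.1 to 1.133 and complete 12-month weights. The documents do not establish that the trial is underpowered for weight. They show that its stated 80% depends on a share that is not given and that would have to exceed the county figure by about 10 to 14 points at 253 per group. Nothing here biases an estimate or affects the type I error rate.

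**What to change.** In Power and sample size considerations:

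- State that 198 means analysable overweight or obese patients per group.
- Give the share of overweight or obese patients expected among those randomised in the two clinics, with its source.
- Restate weight power for the number actually expected. For example: about 72-74% with 253 randomised per group if 64% are overweight or obese, with about 291-310 randomised per group corresponding to 80%.

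In Analyses, word the primary weight hypothesis for overweight and obese patients, as the waist circumference hypothesis already is.

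The cost is a few sentences and possibly a less favourable stated power. No extra patients are required, and neither the design nor the planned test changes.
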